### Sampling Plan

#### Sample Size Determination and Power Analysis

As previously described, we will recruit 1500 individuals from the Prolific platform, with equal allocation to study arms. This sample size is currently the largest number of people for which the Prolific platform can assure national representativeness. We made the decision to recruit a large number of participants because we were unable to locate any baseline studies with which to estimate effect size, so we wanted to be conservative. In addition, although the issue of face masks continues to be a point of public contention, the prevalence of public health mandates related to face masks is lower than those in 2020-2021, which we suspect may serve to suppress the effect size relative to what it would be in the midst of more active social discord focused on that topic. With 80% power (2-tailed test), this sample will allow us to detect small effects at α=.05 (Cohen *d*=0.14) and at corrected α=.01 (Cohen *d*=0.18) for differences of trust in science between treatment and control. In keeping with modern inferential statistical recommendations, we will report all *P* values precisely rather than by threshold [40] and provide a balanced interpretation, especially where .01<*P*<.05.

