### Study Objectives and Hypotheses

Our study will draw conclusions by randomizing a large, nationally representative sample of US adults to view a sample social media post that either (1) shares a cognitive claim from a 2020 study on face masks (control group), or (2) shares the same cognitive claim but also includes a normative claim about what people should do, given the cognitive claim, which is also from that study (intervention group; see Methods). We hypothesize the following (see Table 1):

Hypothesis 1: Overall trust in science and scientists (21-item scale) [18] will be significantly lower in the intervention arm (cognitive and normative claims) than the control arm (cognitive claim only).Hypotheses 2-5: The credibility of the scientist who conducted the study, credibility of the research, trust in the scientific information on the post, and trust in scientific information coming from the author of the post [32] will each be significantly lower in the intervention arm (cognitive and normative claims) than the control arm (cognitive claim only).Preregistered analyses (without hypotheses): We will study the interaction between the study arm and political orientation for each of the 5 preregistered hypotheses.

**Table 1 table1:** Design table.

Question	Hypothesis (if applicable)	Sampling plan (eg, power analysis)	Analysis plan	Interpretation given to different outcomes
What is the effect of intervention arm assignment on overall trust in science and scientists (21-item scale)?	Overall trust in science and scientists (21-item scale) will be significantly lower in the intervention arm than the control arm.	With 80% power (2-tailed test), this sample will allow us to detect small effects at α=.05 (Cohen *d*=0.14) and at corrected α=.01 (Cohen *d*=0.18) for differences between groups.	ANCOVA^a^, incorporating all 9 listed covariates	A significant effect will be interpreted as evidence that the inclusion of normative language caused the change (if the change exists), regardless of direction.

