What is the effect of intervention arm assignment on the credibility of the research, credibility of the scientist who conducted the study, trust in scientific information from the author of the post, and trust in the scientific information on the post?	For hypotheses 2 through 5, each dependent variable will be significantly lower in the intervention arm than the control arm.	With 80% power (2-tailed test), this sample will allow us to detect very small effects at α=.05 (Cohen *d*=0.14) and at corrected α=.01 (Cohen *d*=0.18) for differences between groups.	ANCOVA, incorporating all 9 listed covariates	A significant effect will be interpreted as evidence that the inclusion of normative language caused the change (if the change exists), regardless of direction.
Are there any significant interactions between intervention arm assignment and political orientation on any of the prespecified dependent variables?	N/A^b^	N/A	Linear regression including the interaction between intervention arm and political orientation; the model will include the remaining 8 covariates	A significant interaction will be interpreted as possible evidence that political orientation may mediate or moderate the effect of including normative language in some way, regardless of direction, but that further research is needed.

^a^ANCOVA: analysis of covariance.

^b^N/A: not applicable.

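### The flat corrected level of .01 for five primary outcomes implies single-step Bonferroni; Holm's step-down procedure would hold the same familywise .05 and recover per-outcome power at almost no cost

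*Protocol article*

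**What the plan says.** The Primary Outcomes section lists five outcomes: the 21-item trust scale (Hypothesis 1) and four single items about the post, the research and the scientist (Hypotheses 2 to 5). Study Objectives and Hypotheses gives the same count ("for each of the 5 preregistered hypotheses").

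Sample Size Determination and Power Analysis fixes the sample ("we will recruit 1500 individuals from the Prolific platform, with equal allocation to study arms") and the power basis ("With 80% power (2-tailed test"). It then gives two detectable effects: "detect small effects at α=.05 (Cohen *d*=0.14" "and at corrected α=.01", the latter with d=0.18. Both hypothesis rows of Table 1 repeat this pair of levels; the second row begins "this sample will allow us to detect very small effects at α=.05" and goes on to the same corrected .01.

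The power section adds that P values will be reported exactly and that results between .01 and .05 in particular will get a balanced reading. Table 1 interprets significance outcome by outcome. For the four post-specific items the prediction is individual: "For hypotheses 2 through 5, each dependent variable will be significantly lower in the intervention arm than the control arm".

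No procedure such as Bonferroni or Holm is named anywhere in the article, and the Statistical Analyses section does not return to multiplicity.

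**The concern.** A level of .01 attached alike to each of five tests is .05 divided by five. A zone from .01 to .05 that stays the same whatever the other outcomes show belongs to a single-step rule. Under a step-down rule the boundary moves: a P value of .02 is a rejection at the fourth step (.025) once three others have been rejected.

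Single-step Bonferroni gives up the most power when several effects are real, and that is the pattern the trial predicts. Cognitive and Normative Scientific Claims and Expected Findings both anticipate lower general and post-specific trust and credibility together. Because each outcome is to be judged separately, per-outcome power matters. It cannot be bought with more participants, since the article says 1500 is the largest sample for which the platform can assure national representativeness. The article also suspects that the effect may be suppressed.

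**Working it through.** **Inputs from the article.** 1500 participants at 1:1, so 750 per arm; two-sided tests; 80% power; levels .05 and .01; five hypotheses.

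**Assumed.** Correlation between outcomes (the article gives none): common values of 0, 0.3, 0.5 and 0.7. Normal approximation with SD 1. Any precision gained from the ANCOVA covariates is ignored.

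**Step 1: the article's own figures.** The standard error of d is √(2/750) = 0.0516. Detectable d = (z for the level + z for the power) × standard error.
- Level .05: (1.960 + 0.842) × 0.0516 = 0.1447, stated as 0.14.
- Level .01: (2.576 + 0.842) × 0.0516 = 0.1765, stated as 0.18.

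Both reproduce to two decimals. The noncentral t gives 0.1448 and 0.1767.

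**Step 2: the origin of .01.** .05/5 = .0100 exactly. Šidák's level would be .0102.

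**Step 3: Holm's rule.** Order the five P values and compare them with .05/5, .05/4, .05/3, .05/2 and .05, that is .01, .0125, .0167, .025 and .05, stopping at the first failure. Every threshold is at least .01, so any outcome with P ≤ .01 is rejected under Holm too. When the procedure reaches the first true null, the threshold is at most .05 divided by the number of true nulls, so familywise error is at most .05 whatever the correlation.

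**Step 4: power, fixed .01 against Holm** (200,000 simulated sets of five correlated z statistics per scenario, 750 per arm).

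| Correlation | All d=0.18, per outcome | All d=0.18, all five rejected | All d=0.14, per outcome |
|---|---|---|---|
| 0 | 82% → 92% | 36.9% → 70.5% | 55% → 66-67% |
| 0.3 | 82% → 90% | 47.4% → 74.5% | 55% → 66% |
| 0.5 | 82% → 90% | 54.4% → 77.8% | 55% → 65% |
| 0.7 | 82% → 89% | 61.9% → 81.3% | 55% → 64% |

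The fixed-level figures can be checked by hand: 0.18/0.0516 − 2.576 = 0.91, which gives 82%; 0.14/0.0516 − 2.576 = 0.135, which gives 55%.

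**Step 5: where the gain shrinks or vanishes.**
- Three of five effects at d=0.18: 82% → 85-86% for each real effect.
- One of five at d=0.18: 82% under both.
- Power to reject at least one hypothesis: identical in every scenario, because Holm's first step is also .01.

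**Step 6: error rates.** With no true effects, familywise error is the same for both rules, from 4.9% at correlation 0 to 3.5% at 0.7. If the trust scale is null and the four items each have d=0.20, the scale's own false-positive rate rises from 1% to about 4-4.5% under Holm, within the 5% bound.

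**Step 7: the gain in participants.** At a fixed .01 and d=0.18, 90% power needs 2 × (2.576 + 1.282)² / 0.18² = 919 per arm, or 1,838 in total. Put the other way, if all five effects are equal, the d detectable with 80% per-outcome power falls from 0.177 to about 0.16 under Holm.

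**The case against.** The strongest reply is that nothing here is wrong. A .05/5 level is valid, both detectable effects reproduce, and choosing between two valid familywise methods can look like preference. No procedure is named, and Holm's first step is also .01, so the power statement could stand unchanged under Holm. All of that stands, and it is why the point is an improvement and not an error. Even so, the fixed zone between .01 and .05 fits a single-step rule, and nothing in the article modifies it.

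A second reply is that exact P values and a balanced reading soften the loss. Every result that Holm rejects and the flat rule does not lies in that zone, and with all five P values published a reader could apply Holm. This is true, but a balanced reading is not a decision rule, and Table 1 acts on a significant effect.

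A third reply is that Next Steps is triggered by one or more supported hypotheses, where power does not change. That stands for the dissemination decision. The hypotheses and Table 1, however, make claims outcome by outcome.

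A reader might also infer that the general-trust scale would gain most, for example from 26% to 47-48% power. That figure assumes d=0.10 for the scale and 0.20 for the other four. The article supports neither; it says that no baseline studies for estimating an effect size were found. The predictions give a common direction, not sizes. If all five effects were only d=0.10, per-outcome power would be 26% against 30-32%.

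**Conclusion.** The point holds as a cheap gain in efficiency. The flat .01 implies single-step Bonferroni, by inference from .05/5 and the fixed grey zone and not from a named procedure. Holm keeps the same familywise .05 and never rejects less. If all five effects are real at d=0.18, the gain is about 7 to 10 percentage points per outcome across the correlations tried; at d=0.14 it is about 9 to 11. It is small when few effects are real, and nil for a lone effect or for at least one rejection.

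A reader might infer that the correction is mistaken or that the trial is underpowered because of it. The documents support neither: the level is valid and d=0.18 is correct for it. The power figures rest on assumed correlations, equal effects where stated, and the normal approximation without covariate adjustment. Familywise control under Holm rests on none of these.

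**What to change.** In Sample Size Determination and Power Analysis, and in both hypothesis rows of Table 1, replace the flat corrected level with a statement that the five primary P values will be tested by Holm's procedure at familywise .05. Report Holm-adjusted P values beside the exact unadjusted ones, which keeps the article's aim of precise reporting. Keep d=0.18, described as the detectable effect at the first and strictest Holm step, so the power statement remains correct.

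The cost is one sentence, matching wording in Table 1, and one line of code, with no extra participants. Two downsides should be accepted openly: simultaneous confidence intervals that match Holm are less simple than Bonferroni intervals, and the error rate for a single null outcome can rise above 1%, to about 4-4.5% when the other four effects are real, while familywise error stays within 5%. The change should be made before outcome data are seen.

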#### Technical Exclusion and Inclusion Procedures

With participant recruitment through a web-based pool, the number of usable responses is specified first (ie, the sample size)—in this case, 1500. When participants complete the survey, they will submit evidence of completion to the researchers, who will then approve payment via the Prolific platform. When an individual is rejected for payment (either at the time of submission for payment or at any other time), they will be resampled and replaced by a new member of the pool who matches their sociodemographic characteristics (eg, age, sex, and race/ethnicity). As a result, the number of participants who accept the survey initially will generally be different than the final sample size. This difference can occur for the following reasons (we provide *rough estimates* of prevalence based on a prior large study with the Prolific platform) [20]:

Excluded: refusal to participate by declining consent (approximately 0.19%)Excluded: failing a quality control check and “returning” the survey (approximately 2.14%)Excluded: exiting the Qualtrics platform immediately after consenting to participate (approximately 0.37%)Excluded: exiting the Qualtrics platform prior to accessing the intervention, typically, but not always, after being informed of failing a quality control check (approximately 2.88%)Included: completing the full study correctly but failing to submit a request for payment (approximately 1.58%)

The overall estimated impact is that is roughly 5.57% of individuals who initially access the survey from the study pool will end up being rejected and resampled in the process of reaching the targeted sample size of 1500. Subsequently, a small number of individuals (roughly 1.58%) may fail to submit for payment but otherwise provide good data; these individuals will be analyzed in the arms to which they were assigned (but as noted earlier, will not be allocated 1:1).

### Analysis Plan

#### Primary Outcomes

The primary outcomes are as follows.

Hypothesis 1Overall trust in science and scientists will be measured by the 21-item scale developed and validated by Nadelson et al [18]. An example item from the scale measures agreement with the statement, “When scientists change their mind about a scientific idea it diminishes my trust in their work.” This scale has demonstrated excellent internal reliability in our previous studies with crowdsourced samples (α>.900) [19-22,41].Hypotheses 2 through 5Single-item measures of credibility and trust that are specific to the hypothetical social media post and the scientist who conducted the study, from Song et al [32]“How credible is the scientist who conducted the study described in the post?” (1=not credible at all to 7=extremely credible); note that this language is slightly different than the original item to avoid ambiguity arising from the potential that a scientist authored the social media post“How credible is this research?” (1=not credible at all to 7=extremely credible)“I would trust scientific information if I knew it came from this author.” (1=strongly disagree to 7=strongly agree)“I trust this scientific information.” (1=strongly disagree to 7=strongly agree)

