**Objective:**

The objective of this trial will be to examine if reading normative and cognitive claims about a scientific study, compared to cognitive claims alone, results in lower trust in science and scientists as well as lower perceived credibility of the scientist who conducted the study, perceived credibility of the research, trust in the scientific information on the post, and trust in scientific information coming from the author of the post.

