#### Intervention and Control Description

To isolate the specific effects of normative language in describing scientific findings, we will show participants 1 of 2 fake social media posts depending on the study arm to which they are randomized. The posts will be identical except for the inclusion of normative language in the intervention post. To improve ecological validity [38], both posts will be designed using the formatting parameters for modern Facebook timeline posts as displayed in a web browser using “night” mode (see Figures 2 and 3). The posts will appear as posts “Suggested for you” from a generic science page, which is the primary subheading that Facebook uses when inserting content that is not explicitly followed on a person’s timeline. The lead-in text will read, “Today’s post highlights a study published back in April 2020, right after the COVID-19 pandemic arrived in the United States. This was from a peer-reviewed paper in *Infectious Disease Modeling*.” Both posts will be accompanied by the same generic image of a surgical face mask and a bottle of hand sanitizer.

Additionally, in service of ecological validity, the written content of the graphics will be drawn directly from a highly cited April 2020 paper on face masks for the prospective prevention of COVID-19 [39]. The control post (Figure 2) will feature only a cognitive claim: “Scientists used models based on data from New York and Washington. Their results showed that ‘broad adoption of even relatively ineffective face masks may meaningfully reduce community transmission of COVID-19 and decrease peak hospitalizations and deaths.’”

The intervention post (Figure 3) will include the same cognitive language but also add a normative statement derived from the same source paper. It will add “Based on their findings, the study authors suggested ‘that face mask use should be as nearly universal (i.e., nation-wide) as possible and implemented without delay, even if most masks are homemade and of relatively low quality.’”

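### The outcome labelled as trust in the post's author is measured by an item that says only 'this author' and does not say whose author is meant

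*Protocol article*

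**What the plan says.** The Abstract (Objective and Methods), the hypotheses under Study Objectives and Hypotheses, and Table 1 all name the target of this outcome as the person behind the post. The Objective has "trust in scientific information coming from the author of the post" and Table 1 has "trust in scientific information from the author of the post".

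Primary Outcomes gives the item itself: "I would trust scientific information if I knew it came from this author", rated from 1 to 7. The same list includes an item on the credibility of the study's scientist. The plan says that it changed the source wording of that item "to avoid ambiguity arising from the potential that a scientist authored the social media post". It reports no change to the author item.

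Under Intervention and Control Description, the post comes "from a generic science page". The control text opens "Scientists used models based on data from New York and Washington". The intervention text adds a sentence that begins "Based on their findings, the study authors suggested". The comprehension questions then refer to the study authors once in the question shown to both arms, and once more in the question shown only to the intervention arm.

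**The concern.** The label and the item do not name the same target. A respondent who looks back for an author finds, in the quoted material, only the study's authors. Two things are at stake, both confined to this one outcome.

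- **Construct.** If part of the sample rates the study authors, the item partly repeats the scientist-credibility outcome and measures trust in the poster less cleanly than its label says.
- **Comparison between arms.** The word 'authors' appears more often in the intervention arm. If that changes whom respondents have in mind, part of an arm difference could come from rating a different person. Randomisation does not prevent this, because the change in referent would follow assignment. Table 1 commits to reading a significant effect in either direction as caused by the normative language.

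**Working it through.** **1. Where the word occurs.** Count of 'author(s)' in the participant text quoted in the article, counting the post text once:

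| Text | Control | Intervention | Refers to |
|---|---|---|---|
| Lead-in and cognitive claim | 0 | 0 | – |
| Added normative sentence | – | 1 | study authors |
| Comprehension question, both arms | 1 | 1 | study authors |
| Comprehension question, intervention only | – | 1 | study authors |
| Total | 1 | 3 | study authors |

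No occurrence refers to an author of the post. The comprehension screen also shows a smaller copy of the post, and a wrong answer returns the participant to it. Both would add exposures to the intervention sentence, and neither is counted here.

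**2. The plan's own yardstick.** Inputs from Sample Size Determination and Power Analysis: 1500 participants with equal allocation (750 per arm), 80% power, two-sided test. The detectable effect is d = (z(1−α/2) + z(0.80)) × √(2/750).

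- α = .05: (1.960 + 0.842) × 0.05164 = 0.1447, stated as 0.14.
- α = .01: (2.576 + 0.842) × 0.05164 = 0.1765, stated as 0.18.

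The stated figures are reproduced after rounding.

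**3. What a mixed referent does.** Let p be the share of an arm that reads the item as meaning the study authors, and let g be the gap in mean rating, in SD, between study authors and post author. If p is the same in both arms, the arm difference is p × (effect on trust in the study authors) + (1 − p) × (effect on trust in the post's author). It is a blend of two effects, not the effect that the label names.

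If p differs by arm, and normative language has no effect on trust in either target, the arm difference is still

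shift = (p in intervention − p in control) × g.

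The documents give neither p nor g. Both are assumed here over a range:

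| Difference in p | g = 0.25 SD | 0.50 SD | 0.75 SD | 1.00 SD |
|---|---|---|---|---|
| 5 points | 0.013 | 0.025 | 0.038 | 0.050 |
| 10 points | 0.025 | 0.050 | 0.075 | 0.100 |
| 20 points | 0.050 | 0.100 | 0.150 | 0.200 |
| 30 points | 0.075 | 0.150 | 0.225 | 0.300 |

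The shift runs from about 0.01 to 0.30 SD. Its sign is the sign of g if the extra mentions move respondents towards the study authors. It reaches the detectable effect at α = .05 only towards the far end of the range, for example with a 20-point difference and a 0.75 SD gap (0.20 × 0.75 = 0.15).

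**The case against.** The strongest reply is that context may already settle the referent. Figures 2 and 3 and the on-screen questionnaire are not shown, so a page name, a byline or a lead-in pointing to the post could be present. In the order listed, respondents have just rated the study's scientist, and a different noun suggests a different target. The item is singular, while the cues counted above are plural and tied to the study. These points lower the likely share of misreadings. They do not fix the referent, and the plan itself judged the same ambiguity serious enough to reword the neighbouring item.

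A reader might go further and infer that many respondents will answer about the study authors, or that the wording builds a known bias into the comparison. The documents support neither inference. Control participants also meet the study authors, in their comprehension question, so the arms differ in repetition and not in presence of the cue. One of the two extra mentions is part of the normative sentence and so belongs to the treatment. Nothing shows that moving from one mention to three changes how a later item is read. The direction is open too: if study authors are trusted more than an anonymous page, a shift towards them would raise intervention scores and work against the hypothesis of lower trust.

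Keeping published wording for comparability is a legitimate aim, although the plan does not give that reason here and gave up exact wording for the scientist item.

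**Conclusion.** The mismatch between label and item stands for one of the five primary outcomes. The other four do not use this phrase and are unaffected. In the quoted participant wording the item has no post author to point to, and the remedy applied to the scientist item is not described for this one. Some respondents may rate the study authors, so the outcome may overlap with scientist credibility.

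An artefact that differs by arm is a possibility and not a demonstrated bias. The range of 0.01 to 0.30 SD rests wholly on assumed inputs and shows only that the shift could be anything from negligible to larger than the trial's detectable effects of 0.14 and 0.18. The conclusion also depends on the unseen survey screens: if a lead-in already names the post, the sponsor need only say so.

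**What to change.** Keep the item and replace its last two words, so that it ends *the author of this social media post*. Record the departure from the source item, as was done for the scientist item. If the survey screen already makes the referent explicit, state that in Primary Outcomes instead. Naming the science page would also remove the ambiguity, but it changes the target from an author to a page, so the outcome label would have to change everywhere it appears.

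The cost is a few words in one survey item and slightly less verbatim comparability with the source. Sample size, power and analysis do not change. The Results section says that the protocol was submitted before any recruitment or data collection, so on the document's own account the change could be made in time. Once responses are collected, the ambiguity cannot be removed.
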